#### Additional measures

The following independent (predictor) variables will be assessed prior to surgery at baseline during patient preadmission appointments:Personality: measured using the Big Five Personality Inventory, a 15-item questionnaire [33]Control: measured using the Locus of Control, a 7-item questionnaire [34]Risk Attitudes: single-item scale used in the British Household Panel Survey [35]Optimism: measured using the 10-item Life Orientation Test-revised Questionnaire [36]Fear avoidance beliefs: measured using the 5-item Fear Avoidance Beliefs Questionnaire [37]Catastrophising: measured using the 13-item Pain Catastrophising Scale [38]Charlson Comorbidity Score (CCS) [39]. This is a weighted index for classifying comorbidities’ severity, validated for estimating the risk of morbidity and mortality in longitudinal studiesCharnley classification [40]: stratifies patients by the presence of arthritis in one or more large joints; a condition that impairs walking; previous total joint arthroplasty (TJA) on the contra-lateral knee and/or hipsBaseline radiographic disease severity as assessed by the Kellgren-Lawrence grading [41]

### Timelines

This is a 1-year study with an anticipated start date of February 2016 and end date of January 2017. See Table 3 for SPIRIT schedule of study including enrolment, interventions and assessments.

**Table 3 Tab3:** SPIRIT trial study schedule

Activity/assessment	Enrolment	Randomisation	*t* _*1*_	*t* _*2*_	*t* _*3*_	*t* _*4*_
	−*t* _*1*_	0				
Baseline data, demographics	X					
Eligibility screen	X					
Informed consent	X					
Randomisation		X				
Baseline assessments battery^a^			X			
Expectation survey^b^				X		
Total knee arthroplasty					X	
12-month assessments^c^						X

^a^Baseline assessments will be given to patients during their preadmission appointments and completed with the assistance of the study coordinator. Assessment items include: Western Ontario and McMaster Universities (WOMAC) Osteoarthritis Index; Veterans RAND Health Survey mental component score (VR-12); Big Five Personality Inventory; Locus of Control; Risk Attitudes; Hospital for Special Surgery: Knee Surgery Expectations Survey; Fear Avoidance Beliefs Questionnaire; Pain Catastrophising Scale; Life Orientation Test-revised Questionnaire; and the DCE survey for patients in the intervention group

^b^Patients will complete the Hospital for Special Surgery: Knee Surgery Expectations Survey 1 week prior to scheduled TKA via phone with study coordinator

^c^12-month assessment will be given to patients at their 1-year post-TKA surgical review visit. Assessments include: WOMAC; VR-12 (this assessment is routine for all patients undergoing TKA)

### Sample size

Intervention effectiveness will be evaluated by comparing change in the primary outcome measure between groups. We aim to detect minimum clinically important improvement (MCII) in the WOMAC. The sample size calculation was based on the following parameters: (1) an alpha value = 0.05, two-sided; (2) power = 80 %. To demonstrate a minimum clinically important difference in WOMAC scores of 15 points (SD [42]), between groups, the sample size required for each group is 45.

To demonstrate a difference in satisfaction the sample size calculation was based on the following parameters: (1) an alpha value = 0.05, two-sided; (2) power = 80 %; (3) expected rates of satisfaction at 1 year post TKA of 77 % for patients in the intervention arm prior to consenting to surgery compared to 51 % for patients undergoing standard procedural consent. The expected rates of satisfaction are derived from a recent study which reported 49 % of patients whose expectations were not met reported dissatisfaction with their TKA compared 6 % of patients whose expectations were met [13]. Incomplete data were reported in 17 % of the patient cohort and, therefore, these patients were not included in the analysis. We have, therefore, assumed a worst case scenario that these 17 % would have reported dissatisfaction despite having their expectations met. Based on these rates the sample size required in each group is 60. To allow for a 10 % dropout of patients, we will recruit 132 patients in total (66 per arm). This estimate is conservative based on our prior RCTs in TKA [43, 44], where we have achieved >95 % retention at 12 months.

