### Recruitment

Patients will be approached about participation in the study after consent for TKA, but before surgery. We chose to administer the DCE activity post consent for surgery so as to maintain surgeon blinding and avoid any influence the DCE activity may have on the consent process itself. It is possible but unlikely that completing the DCE activity may influence the decision to undergo TKA. Since we are using an intent-to-treat design, should this occur our statistical analyses will account for missing data by using multiple imputations. Potential patients waitlisted for TKA identified as meeting the inclusion criteria will receive both verbal and written information about the requirements for participation including: (1) verbal explanation of the project by the study coordinator upon initial contact during their attendance at the orthopaedic preadmission clinic at SVHM, (2) a detailed outline of the project content and required commitment in the Patient Information and Consent Form (see Additional file 2: Participant Information and Consent Form). Patients agreeing to take part in the trial will be required to provide written informed consent. Informed consent will be obtained by the research associate only after the patient has read and fully understands the details of the project.

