## Discussion

The outcomes of patients following TKA are beneficial on average; however, research demonstrates that patient dissatisfaction following TKA is between 15 and 30 % [13]. One of the strongest predictors of patient dissatisfaction following TKA is unmet patient expectations [21], suggesting a misalignment between patients and surgeons during the procedural consent process. Therefore, it is important to assess patients’ preferences of acceptable risk in undergoing TKA to reduce pain or improve function, which has largely been unexplored. This project aims to use DCEs to explore patient risk-benefit preferences of surgery, and will use a RCT to determine whether applying a DCE prior to surgery improves patient expectations, health outcomes and satisfaction.

DCEs are one of the most commonly used techniques for assessing patients’ preferences in the health care domain. The current research is the first to use a DCE as an intervention to improve patients’ knowledge about the outcomes of a health care intervention. DCEs are not only a useful way to present information, but also require patients to engage through the process of making trade-offs. This may help to ensure that the information presented is more readily absorbed by patients as opposed to simply reading an information leaflet. In recent years there has been an increasing emphasis on the importance of patient involvement in medical decision-making [46–48]. These interventions can improve outcomes by aligning patient and surgeon expectations of surgery, which promotes greater patient satisfaction and increases patient compliance [49].

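### The satisfaction sample size uses subgroup rates (expectations unmet v met) as arm rates; with the document's own overall dissatisfaction figures, the claimed 80% power is not supported

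*Protocol article*

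**What the plan says.** Satisfaction is one of two primary outcomes (Outcome assessments). Its calculation, at two-sided alpha 0.05 and 80% power, takes "expected rates of satisfaction at 1 year post TKA of 77 % for patients in the intervention arm", "compared to 51 % for patients undergoing standard procedural consent". The source is then given: "The expected rates of satisfaction are derived from a recent study which reported" 49% dissatisfied among patients whose expectations were not met and 6% among those whose expectations were met. The 17% of that cohort with incomplete data are counted as dissatisfied despite met expectations. The result is 60 per group, raised to 66 per arm and 132 in total for dropout. The WOMAC calculation needs only 45 per group, so satisfaction sets the size of the trial.

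Elsewhere the article describes unselected TKA patients. The Discussion says "research demonstrates that patient dissatisfaction following TKA is between 15 and 30" per cent. The Background gives the same range, and both cite the reference used in the sample size. The Abstract goes as high as one in three.

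On timing, the Sample size section attaches its 77% to a rate "for patients in the intervention arm prior to consenting to surgery compared to" standard procedural consent, whereas Recruitment says: "We chose to administer the DCE activity post consent for surgery".

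**The concern.** The two planning rates belong to groups defined by whether expectations turned out to be met, not to groups formed by randomisation. Using them as arm rates treats every control patient as having unmet expectations and every DCE patient as having met ones. An unselected control arm is a mixture. A control rate of 51% means 49% dissatisfied, which is above every overall figure in the article. The planned DCE rate of 77% (23% dissatisfied) lies inside the article's own usual-care range.

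This calculation fixes the 132. If its power is much lower than stated, a non-significant satisfaction result could be taken as evidence against an effect that the trial had little chance of detecting.

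**Working it through.** **Inputs from the article.** Dissatisfaction 49% (unmet) and 6% (met); 17-point deduction; overall dissatisfaction 15–30%, at most one in three; two-sided alpha 0.05; power 80%; 1:1 allocation; 60 analysed per arm.

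**1. Where the rates come from.** Control: 100 − 49 = 51%. Intervention: 100 − 6 − 17 = 77%. The deduction is made in the intervention arm only.

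**2. Reproducing the 60.** With d = 0.26 and mean rate 0.64:

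n = [1.96·√(2·0.64·0.36) + 0.8416·√(0.51·0.49 + 0.77·0.23)]² / 0.26² = 52.3, so 53 per arm.

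With continuity correction: (52.3/4)·[1 + √(1 + 4/(52.3·0.26))]² = 59.8, so 60 per arm. Power at 60 is 80.2% corrected and 85.2% uncorrected. The plan's figure is therefore the continuity-corrected one, and its arithmetic is sound.

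**3. Control rate implied by the article.** 100 − 30 = 70% to 100 − 15 = 85%; with one in three dissatisfied, 66.7%.

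**4. Power at 60 per arm with the plan's 77% kept.** Power = Φ{[d√n − 1.96√(2p̄(1−p̄))] / √(p₁(1−p₁) + p₂(1−p₂))}. For the corrected value, replace n by n(1 − 1/(nd))².

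| Control | DCE arm | Uncorrected | Corrected |
|---|---|---|---|
| 66.7% | 77% | 24% | 18% |
| 70% | 77% | 14% | 10% |
| 75% | 77% | 4% | 3% |
| 77% or more | 77% | no benefit assumed | no benefit assumed |

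**5. Treating the control arm as a mixture.** If a share u has unmet expectations, dissatisfaction is 0.06 + 0.43u. Setting this to 0.15 and 0.30 gives u = 0.09/0.43 = 21% and 0.24/0.43 = 56%. The article states neither u nor how far the DCE would reduce it, so two assumptions are shown.

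*Assumption A: the DCE meets every patient's expectations, and 94% are satisfied (no 17-point deduction).*

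| Control | DCE arm | Uncorrected | Corrected |
|---|---|---|---|
| 85% | 94% | 36% | 26% |
| 80% | 94% | 63% | 52% |
| 75% | 94% | 83% | 75% |
| 70% | 94% | 94% | 90% |
| 66.7% | 94% | 97% | 95% |

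*Assumption B: the DCE halves the unmet share.* The gain is 0.43u/2, which is 4.5 to 12 points over the 15–30% range.

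| Control | DCE arm | Uncorrected | Corrected |
|---|---|---|---|
| 85% | 89.5% | 11% | 7% |
| 80% | 87% | 18% | 12% |
| 75% | 84.5% | 25% | 18% |
| 70% | 82% | 34% | 26% |

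**6. Difference detectable with 80% power at 60 per arm, continuity-corrected.** From 70%: about 91.6%. From 77.5%: about 96.2%. From 85%: only virtually 100%.

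**7. A 10-point gain.** Corrected power is 18% (70 v 80%), 22% (77.5 v 87.5%) and 33% (85 v 95%).

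**The case against.** Three stronger readings are tempting, and the article does not support them.

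- A reader might infer a calculation error. There is none: 60 per arm follows from the stated rates.
- A reader might infer that a 26-point difference is impossible on the article's own figures. Over 15–30% dissatisfaction, full conversion gains 9 to 24 points. At one in three it gains 33.3 − 6 = 27.3 points. So the difference can arise, but only at the article's highest figure and with every unmet expectation removed.
- A reader might infer that 80% power is out of reach in every case. Power depends on the rates as well as the gap, and full conversion from a 70% control rate gives 94% (90% corrected).

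Other points on the plan's side carry some weight. The 17-point deduction makes the assumed effect smaller, so it is cautious in intent. It does nothing to correct the 51%, and beside a realistic control rate it leaves little or no effect. The halving scenario is an assumption of this review. The mixture treats the 15–30% and the 49%/6% as one population with one definition of satisfaction, although the trial uses the SAPS and the cited study cannot be checked here. That limits the precision of step 5. The mismatch between 51% and the article's overall figures does not depend on it. The WOMAC outcome has its own sample size and is untouched.

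**Conclusion.** The point holds as a fault in the planning assumptions. The 51% control rate describes only patients with unmet expectations and conflicts with the article's implied 67–85%. With the plan's own 77% kept, power at 60 per arm is at most about 24% (18% corrected). It is about 14% (10% corrected) at the lower end of the 70–85% range and disappears from 77% upward. About 80% power or more would survive only if usual-care dissatisfaction were roughly 25–30% or higher and the DCE met every patient's expectations with 94% satisfied. The plan does not assume this. If the DCE halved unmet expectations, power would be 11–34% (7–26% corrected).

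The consent wording is a separate inconsistency. It does not affect these power figures, but the contrast described in the Sample size section is not the one the trial makes, since Recruitment places the DCE after consent to surgery.

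**What to change.** Keep 132 patients and revise the Sample size section:

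- Replace the 51%/77% basis with a control rate taken from the article's 15–30% dissatisfaction, or from the centre's registry if it records satisfaction. Add an explicit assumption about how far the DCE reduces unmet expectations.
- Withdraw the claim of 80% power for 77% v 51%.
- Print the difference detectable with 80% power at 60 analysed per arm, on the same continuity-corrected basis as the 60: about 70% to 91.6%, 77.5% to 96.2%, and from 85% only virtually 100%. Rounder targets should not be used: 70% to 90% has 79% power uncorrected and 72% corrected.
- State that a non-significant satisfaction result does not exclude gains of about 10 points.
- Separately, reconcile the statement that places the intervention before consent to surgery with Recruitment.

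The cost is rewording and a less favourable power statement. No extra patients are needed, and the design and analysis do not change.

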### Recruitment

Patients will be approached about participation in the study after consent for TKA, but before surgery. We chose to administer the DCE activity post consent for surgery so as to maintain surgeon blinding and avoid any influence the DCE activity may have on the consent process itself. It is possible but unlikely that completing the DCE activity may influence the decision to undergo TKA. Since we are using an intent-to-treat design, should this occur our statistical analyses will account for missing data by using multiple imputations. Potential patients waitlisted for TKA identified as meeting the inclusion criteria will receive both verbal and written information about the requirements for participation including: (1) verbal explanation of the project by the study coordinator upon initial contact during their attendance at the orthopaedic preadmission clinic at SVHM, (2) a detailed outline of the project content and required commitment in the Patient Information and Consent Form (see Additional file 2: Participant Information and Consent Form). Patients agreeing to take part in the trial will be required to provide written informed consent. Informed consent will be obtained by the research associate only after the patient has read and fully understands the details of the project.

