#### DCE experimental design

The six attributes and corresponding levels described in Table 1 give rise to a possible combination of 729 (3^6^) treatment outcome scenarios. As this full factorial design of possible scenarios was not feasible to present to each patient, a sample was generated using a fractional factorial experimental design. An efficient design was generated using NGENE software, such that attributes were varied independently from one another across the scenarios and that standard errors were minimised. This model allows for multiple versions of the questionnaire, reducing the burden on patients and increasing the statistical efficiency of the study. Two versions of the DCE questionnaire were generated, each containing six different choice sets. Each DCE questionnaire had the same number of scenarios with the same attributes, but different attribute levels in each questionnaire. The sample of scenarios were then organised into pairwise profiles labelled ‘Choice A’ and ‘Choice B’, and participants were asked to choose between the pair of choices in each of the six choice sets. Furthermore, an opt-out option was included at the end of each choice set where patients were asked if, given the scenarios presented, they would still have the operation or prefer to remain in their current health state. This opt-out option was included as it reflects the voluntary nature of elective TKA in real life. For an example of a discrete choice task see Table 2.

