### Outcome assessments

#### Data capture

Demographic information collected at baseline will include age, gender, comorbidities, body mass index and socioeconomic data.

***Primary outcomes***: will be (1) changes in patient-reported knee pain and disability between baseline and 12 months post TKA, and (2) patient satisfaction.

Pain and physical function will be measured on the WOMAC Osteoarthritis Index [27]. The WOMAC consists of 24 items covering three subscales: pain (five items), stiffness (two items) and physical function (17 items). The pain and physical function subscales will be used, each subscale transformed to a score ranging from 0 to 100, with a higher score indicating greater pain and physical function. The WOMAC is a widely used questionnaire specifically designed to evaluate knee and hip OA [30, 31]. Patient satisfaction will be derived from the Self-administered Patient Satisfaction Scale (SAPS) for primary knee arthroplasty, a validated self-administered patient satisfaction scale [30]. Patients will be mailed both questionnaires at 12 months and patients who do not attend review clinics will complete the post-TKA surveys via phone call from a study coordinator, who will be blinded to intervention allocation.

***Secondary outcomes***: will be (1) changes in patient-reported psychological wellbeing between baseline and 12 months post TKA. Psychological wellbeing will be derived from the 12-item short form version of the Veterans RAND Health Survey mental component score (VR-12) [31], (2) differences in expectations of recovery between baseline and 1 week prior to scheduled TKA for patients in the intervention arm. Recovery expectations following TKA will be measured using the 19-item Hospital for Special Surgery: Knee Surgery Expectations Survey [32]. This measure forms a part of the larger study survey, but is measured before patients complete the DCE component, (3) concordance between matched surgeon and patient expectation for recovery following TKA. Surgeons will complete the same expectation survey as patients immediately following consultation and consent for surgery. The surgeon and patient expectation survey will then be paired for analysis.

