### Statistical analysis

Statistical analysis will be by intention-to-treat. Categorical variables will be analysed using chi-squared tests (or Fisher’s exact test for small samples) while continuous variables will be analysed using *t* tests (parametric) and Mann-Whitney (non-parametric) tests for symmetrically and asymmetrically distributed data, respectively. The significance of differences in dichotomous data will be tested using generalised estimating equations or a linear mixed model. If there are chance imbalances in baseline patient characteristics hypothesised to influence the main outcomes, then statistical techniques that allow adjustment for confounding variables will be used as secondary analyses. DCE data will be analysed based on extensions to logistic regression, including multinomial logit models, mixed logit models and generalised multinomial logit models [45]. If there is more than 5 % missing data, sensitivity analysis allowing for different assumptions, such as the best or worst possible scenario, will also be reported for the main outcomes of the study. Cohen’s kappa coefficient will be used to assess concordance between surgeon and patient expectations.

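### Patients whom the DCE leads not to have TKA are to be multiply imputed as missing data, which with standard imputation would not estimate the intention-to-treat effect that the plan cites as its reason

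*Protocol article*

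**What the plan says.** The Recruitment section of the protocol article explains that the DCE is given after consent to surgery, and then admits a side effect: "It is possible but unlikely that completing the DCE activity may influence the decision to undergo TKA". It gives the handling in the next sentence, with intention-to-treat as the reason: if this happens, "our statistical analyses will account for missing data by using multiple imputations".

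Three other places bear on this rule:

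- **DCE experimental design.** Each of the six choice sets ends by asking whether, given the scenarios, "they would still have the operation or prefer to remain in their current health state". Experimental design says that the control survey does not contain the DCE activity.
- **Data capture and Timelines.** The primary outcomes are "changes in patient-reported knee pain and disability between baseline and 12 months post TKA, and (2) patient satisfaction". Satisfaction is measured with the "Self-administered Patient Satisfaction Scale (SAPS) for primary knee arthroplasty". The footnote to the study schedule says that the "12-month assessment will be given to patients at their 1-year post-TKA surgical review visit".
- **Statistical analysis.** If more than 5 % of data are missing, the plan adds "sensitivity analysis allowing for different assumptions, such as the best or worst possible scenario" for the main outcomes.

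**The concern.** A value is missing when it exists, or would exist under the plan, and was not obtained. A patient who decides against surgery because of the DCE is in a different position: the intervention has changed what happened to that patient. Intention-to-treat asks for the outcome the patient actually had under the assigned arm. WOMAC and VR-12 can be observed in someone who was not operated on. Satisfaction with an arthroplasty cannot, because there was none.

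As written, the rule puts such patients together with those lost to follow-up. Because outcomes are scheduled only after TKA, an ordinary imputation model has only operated patients to learn from. It would give the unoperated patients values resembling surgical results. The Background section states that TKA improves pain, disability and quality of life on average, so this would tend to flatter whichever arm has more patients who did not proceed. The plan itself links the event to the DCE.

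**Working it through.** **Inputs from the protocol article (Sample size).** Satisfaction 77 % in the DCE arm and 51 % in the control arm; two-sided alpha 0.05; power 80 %; 60 per arm, raised to 66; WOMAC target difference 15 points.

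**Assumptions, because the article gives no figure.** The number k of DCE-arm patients who decline because of the DCE is varied from 1 to 7 of 66. Surgery is assumed to gain 20–40 WOMAC points, with no change without surgery. Imputation is assumed to return the operated patients' average. The control arm is assumed to be unaffected.

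**The plan's own figure.** The two-proportion formula for 77 % against 51 % gives 53 per arm without continuity correction and 60 with it. The second matches the plan, and 60 × 1.10 = 66. The sample size is not in dispute.

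**Satisfaction.** Imputation at the operated rate leaves the DCE arm at 77 % and the difference at 77 − 51 = 26 points, whatever k is. If decliners are counted as not satisfied, the rate is 0.77 × (66 − k)/66, so each decliner moves it by 0.77/66 ≈ 1.2 points.

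**WOMAC.** The shift in the DCE-arm mean is gain × k/66. For k = 3 this is 20 × 3/66 = 0.9 to 40 × 3/66 = 1.8 points.

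| k | share of DCE arm | share of all 132 | satisfaction, decliners not satisfied | difference from 51 % | shift from 77 % | WOMAC shift (points) |
|---|---|---|---|---|---|---|
| 1 | 1.5 % | 0.8 % | 75.8 % | 24.8 | 1.2 | 0.3–0.6 |
| 3 | 4.5 % | 2.3 % | 73.5 % | 22.5 | 3.5 | 0.9–1.8 |
| 6 | 9.1 % | 4.5 % | 70.0 % | 19.0 | 7.0 | 1.8–3.6 |
| 7 | 10.6 % | 5.3 % | 68.8 % | 17.8 | 8.2 | 2.1–4.2 |

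At k = 3, the 4.5 % is the share of the arm whose satisfaction would be imputed. The shift in the rate is smaller: 77.0 − 73.5 = 3.5 points.

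**The 5 % trigger.** The plan does not say whether the 5 % is taken over an arm or over the whole trial. With no other missing data, three decliners (4.5 % of the arm, 2.3 % of the trial) trigger nothing on either reading. Six decliners trigger it on the arm reading (9.1 %) but not on the whole-trial reading (6/132 = 4.5 %).

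**The case against.** The strongest reply is that the article names multiple imputation in one clause and specifies no model. A reader might infer that decliners will certainly be credited with typical surgical results. The text does not say so: imputation can be run under not-at-random assumptions, and the values assigned could lie below the arm average. It also does not say that scores obtained from unoperated patients would be discarded. This stands, and the point is therefore conditional on standard imputation.

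A reader might also infer that all non-proceeding would fall in the DCE arm. The documents do not support that. Control patients may cancel too, and both arms are recruited at a preadmission clinic where patients are medically optimised. The opt-out items concern hypothetical scenarios put to people who have already consented to surgery, and the plan calls an effect on the decision unlikely. Only an excess caused by the DCE is selective.

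The treatment of satisfaction is partly a choice of estimand. The study aim speaks of outcomes following TKA, for which an as-if-operated estimand could be defended. Counting an informed decliner as not satisfied is a convention that works against the DCE. Satisfaction among operated patients conditions on something that happened after randomisation. All of this stands, and it is why the composite is proposed below only as a sensitivity analysis. An as-if-operated estimand is nevertheless not the intention-to-treat effect on which the plan rests its rule.

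Finally, the best/worst-case analysis overlaps with part of the remedy, since a worst case for the DCE arm counts its decliners as not satisfied. But it applies only above 5 % missing, may not be triggered at plausible counts, and leaves the primary rule as it is.

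**Conclusion.** The point holds in conditional form. The article states a rule that treats a possible effect of the intervention as missing data, and justifies it by intention-to-treat. Under standard imputation the rule would estimate a hypothetical effect instead, and any DCE-induced excess of non-proceeding would tend to favour the DCE arm.

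The likely size is modest. With 3 of 66 declining, it is about 0.9–1.8 WOMAC points against a 15-point target, and at most about 3.5 percentage points of a planned 26-point satisfaction difference. With one decliner it is about 1 point of satisfaction. It becomes material only if the event is less rare than the plan expects: with 7 of 66, the satisfaction difference would be 17.8 rather than 26 points. These figures rest on the assumed counts, the assumed surgical gain, imputation at the operated average, and decliners counted as not satisfied. The rule should be changed, but the documents do not show that the trial's result would be seriously distorted.

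**What to change.** Separate patients who did not have TKA from patients whose outcome was not obtained:

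1. For every randomised patient who does not have TKA, in either arm, collect WOMAC and VR-12 at 12 months after the scheduled surgery date. Use the blinded phone route that Data capture already provides for patients who miss review clinics. Analyse the observed values as randomised.
2. Report the number not proceeding to TKA by arm.
3. Do not impute SAPS for these patients as if they had been operated on. Report satisfaction with them counted as not satisfied as a prespecified sensitivity analysis, whether or not the 5 % trigger is met. Give the result in operated patients beside it, labelled as conditional on surgery.
4. Reserve multiple imputation for values that exist but were not obtained.

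The cost is a few extra phone calls and a paragraph in the analysis section. The estimate may come out slightly less favourable to the DCE.
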